## Abstract

**Background:**

Advances in paediatric cardiology have improved the prognosis of children with inherited cardiac disorders. However, health-related quality of life (QoL) and physical activity have been scarcely analysed in children with inherited cardiac arrhythmia or inherited cardiomyopathy. Moreover, current guidelines on the eligibility of young athletes with inherited cardiac disorders for sports participation mainly rely on expert opinions and remain controversial.

**Methods:**

The QUALIMYORYTHM trial is a multicentre observational controlled study. The main objective is to compare the QoL of children aged 6 to 17 years old with inherited cardiac arrhythmia (long QT syndrome, Brugada syndrome, catecholaminergic polymorphic ventricular tachycardia, or arrhythmogenic right ventricular dysplasia), or inherited cardiomyopathy (hypertrophic, dilated, or restrictive cardiomyopathy), to that of age and gender-matched healthy subjects. The secondary objective is to assess their QoL according to the disease’s clinical and genetic characteristics, the level of physical activity and motivation for sports, the exercise capacity, and the socio-demographic data. Participants will wear a fitness tracker (ActiGraph GT3X accelerometer) for 2 weeks. A total of 214 children are required to observe a significant difference of 7 ± 15 points in the PedsQL, with a power of 90% and an alpha risk of 5%.

**Discussion:**

After focusing on the survival in children with inherited cardiac disorders, current research is expanding to patient-reported outcomes and secondary prevention. The QUALIMYORYTHM trial intends to improve the level of evidence for future guidelines on sports eligibility in this population.

*Trial registration* ClinicalTrials.gov Identifier: NCT04712136, registered on January 15th, 2021 (https://clinicaltrials.gov/ct2/show/NCT04712136).

## Background

Prognosis of children with congenital cardiac disorders has significantly improved in the past two decades, due to great advances in prenatal screening, intensive neonatal care and modern invasive therapies [1]. As a result, more attention has been recently given to health-related quality of life (QoL) and secondary prevention in paediatric cardiology [2, 3].

Traditionally, congenital cardiac disorders are divided into 3 groups: congenital heart disease (CHD) for structural cardiac anomalies, inherited cardiac arrhythmia and inherited cardiomyopathy. So far, QoL studies in paediatric cardiology have mainly focused on the group of children with CHD and, although the overall level of QoL is good in this population, our group highlighted the existing correlation between exercise capacity and QoL, and the risk for physical deconditioning, even for non-serious CHD [4, 5]. Indeed, despite the promotion of physical activity in the current guidelines [6–8], many children with CHD experience social barriers to physical activity and “remain on the side-line” at school or in their social life [9]. Ultimately, these patients may be exposed to the consequences of a sedentary lifestyle: overweight, high blood pressure, social exclusion, and impaired QoL [10–12]. Conversely, patients with CHD who have been physically active since childhood are less likely to become sedentary adults [13].

Such consistent data are not available in the literature for children from the two other groups, e.g. inherited cardiac arrhythmia or inherited cardiomyopathy, for which QoL and physical activity have been rarely studied. Some heterogeneous data were provided from small paediatric [14–16] or adult [17, 18] cohorts, however no prospective controlled study has analysed the determinants of QoL and the level of physical activity in children with inherited cardiac disorders [19]. We hypothesized that QoL scores and physical activity levels in children with inherited cardiac disorders are reduced compared to the healthy subjects.

Therefore, the multicentre observational controlled QUALIMYORYTHM trial aims to evaluate the QoL, exercise capacity, and the level of physical activity of children with inherited cardiac arrhythmia or inherited cardiomyopathy, in comparison with a matched control population. This study will also evaluate the main factors associated with QoL in this population.

## Methods

### Objectives

The main objective of the QUALIMYORYTHM trial is to compare the QoL of children aged 6 to 17 years old with inherited cardiac arrhythmia or inherited cardiomyopathy to that of matched healthy children.

The secondary objective is to assess, in this population, the QoL according to the disease clinical and genetic characteristics, the level of physical activity, the exercise capacity, and the socio-demographic data.

### Study design

The QUALIMYORYTHM trial is a prospective, multicentre controlled observational study with a follow-up of 2 weeks and a recruitment duration of 18 months. All screened subjects will be identifiable throughout the study by a unique subject number. The eligible patients will be divided into 2 groups (Fig. 1):

**Fig. 1 Fig1:**
[figure not shown]
Flow chart

Group 1: children aged 6 to 17 years old with an inherited cardiac arrhythmia or an inherited cardiomyopathy.

Group 2: age and gender-matched control group, with healthy children aged 6 to 17 years old.

### Setting

Patients will be recruited during a paediatric cardiology consultation among the French expert centres for inherited cardiac arrhythmia or an inherited cardiomyopathy (CARDIOGEN national network, http://www.filiere-cardiogen.fr). Overall, 7 university hospitals, labelled as expert centres in paediatric inherited cardiac disorders by health authorities, will participate in patient recruitment.

Conduct of the study will be led by the principal investigator (supported, when necessary, by the co-investigators), a research fellow, and a clinical research coordinator, all of whom are trained in Good Clinical Practice and in the requirements of the study protocol.

### Study population

Children aged of 6 to 17 years old with an inherited cardiac arrhythmia (long QT syndrome, Brugada syndrome, catecholaminergic polymorphic ventricular tachycardia, or arrhythmogenic right ventricular dysplasia), or those with an inherited cardiomyopathy (hypertrophic, dilated, or restrictive cardiomyopathy), will be prospectively recruited during their annual follow-up.

The age- and gender-matched control group will be defined using the same method as in our previous paediatric exercise test studies [4, 5, 20–22]. Children aged 6 to 17 years old referred to the paediatric cardiology consultation for a non-severe functional symptom linked to exercise (murmur, palpitation, or dyspnoea) or for a medical sports certificate will be assessed for eligibility. These children will be classified in the control group only after a completely normal check-up, including physical examination, electrocardiogram, and echocardiography. Children with any chronic disease, medical condition (cardiac, neurologic, respiratory, muscular, or renal), or medical treatment and those requiring any further specialized medical consultation will not be eligible.

Patients who are not able to answer the quality of life questionnaire (e.g. non-French speakers, severe mental illness) will not be eligible for the study. Detailed inclusion and exclusion criteria are reported in Table 1.

**Table 1 Tab1:** Trial entry

Inclusion criteria
Male or female aged 6 to 17 years old
Group 1: Patients with an inherited cardiac arrhythmia (long QT syndrome, Brugada syndrome, catecholaminergic polymorphic ventricular tachycardia, or arrhythmogenic right ventricular dysplasia), or those with an inherited cardiomyopathy (hypertrophic, dilated, or restrictive cardiomyopathy) Group 2: Children with a completely normal check-up, referred to the paediatric cardiology consultation for a non-severe functional symptom linked to exercise (murmur, palpitation, or dyspnoea) or for a medical sports certificate
Informed consent of parents or legal guardians, and oral assent of children
Exclusion criteria
Patients who are not able to understand or fill out the questionnaires (QoL, physical activity and motivation questionnaires) Absolute contraindications for CPET: fever, uncontrolled asthma, respiratory failure, acute myocarditis or pericarditis, uncontrolled arrhythmias causing symptoms or haemodynamic compromise, uncontrolled heart failure, acute pulmonary embolus or pulmonary infarction, and children with mental impairment leading to inability to cooperate Group 2: Children with any chronic disease, medical condition (cardiac, neurologic, respiratory, muscular, or renal), or medical treatment and those requiring any further specialized medical consultation

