### Sample size

We aim to recruit a total of 214 children in both groups. The primary outcome is the difference in the self-reported QoL score with the PedsQL instrument between the children with inherited cardiac disorders and the control group. We used the results from our previous QoL cross-sectional studies in patients with CHD to calculate the sample size [4, 21, 26–29, 39]. In our experience, as well as in similar studies using patient related outcomes, a difference of less than 5 points is not clinically relevant, and a difference of more than 10 points is ideal, but rarely achieved [2, 27, 29]. Therefore, we hypothesized to observe a difference in the total QoL score of 7 ± 15 points (over 100). With a 90% power, a bilateral alpha risk of 5%, and potentially 10% of loss to follow-up or missing data on the primary outcome, we need to include 107 patients in the group 1 and 107 patients in the group 2.

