### Statistical analysis

Patients’ characteristics will be presented using mean and standard deviation for continuous variables, and frequencies and proportions for categorical variables. QoL scores will be calculated with the parametric Student’s t test when the distribution was Gaussian and with the Mann–Whitney test otherwise. The effect size will be estimated using Cohen’s d measure.

Association between QoL scores and physical activity, clinical and socio-demographic data will be studied using Pearson’s or Spearman’s coefficient. According to the type of relation between QoL scores and these factors, a multiple linear regression or a generalized additive model (GAM) will be implemented for the different scores. In the GAM, a parametric portion of the model could be identified (with the vector of parameters associated with the set of explanatory variables). The non-parametric part of the model could be formed by smooth functions for clinical characteristics or age effects for example. One of the main advantages of the GAM implemented is the possibility to address the issue of linear dependency (i.e. collinearity) between these characteristics or age effects which often impedes their simultaneous estimation.

When considering multiple comparisons, the type I error will be adjusted.

The statistical significance will be set at 0.05 and analyses will be performed using Statistical Analysis Systems version 9 (SAS Institute, Cary, NC, USA). Data will be managed by the clinical research unit of Montpellier University Hospital, France, in collaboration with the paediatric and congenital cardiology department.

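### Affected siblings may enter Group 1, but the sample size and every named analysis treat children as independent; this matters mainly for factors that siblings share

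*Protocol article*

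**What the plan says.** **Entry.** Under Study population, Group 1 children "will be prospectively recruited during their annual follow-up". The Setting section places recruitment in seven expert centres for inherited paediatric cardiac disorders. The text states that "Detailed inclusion and exclusion criteria are reported in Table 1". The Group 1 criterion there covers "Patients with an inherited cardiac arrhythmia (long QT syndrome, Brugada syndrome, catecholaminergic polymorphic ventricular tachycardia, or arrhythmogenic right ventricular dysplasia", followed by the inherited cardiomyopathies. Neither the table nor the text restricts entry to index cases or to one child per family.

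**Sample size.** The assumptions are "we hypothesized to observe a difference in the total QoL score of 7 ± 15 points (over 100", then "With a 90% power, a bilateral alpha risk of 5" per cent, with "potentially 10% of loss to follow-up or missing data on the primary outcome". The result is "we need to include 107 patients in the group 1 and 107 patients in the group 2".

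**Analysis.** Under Statistical analysis, "QoL scores will be calculated with the parametric" Student's t test, or with the Mann–Whitney test if the distribution is not Gaussian. Determinants of quality of life are studied by Pearson or Spearman coefficients, then by multiple linear regression or a generalized additive model (GAM). The section discusses collinearity between covariates but not dependence between children.

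**Factors studied.** The secondary objective relates quality of life to genetic and socio-demographic characteristics, among others. Other data collection lists the genetic anomaly and the socio-economic status of the family. Under Secondary outcomes, both parents may each complete a proxy questionnaire. Study design gives each child an individual study number and mentions no family link.

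**The concern.** The Group 1 disorders run in families, and recruitment is at the clinics where affected families are followed. Two affected siblings aged 6 to 17 could both be eligible, and nothing stated prevents both from entering. Siblings share a household, often the same variant, and the parents who complete the proxy forms. Their scores may therefore be positively correlated.

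A two-sample calculation, a t or Mann–Whitney test, simple correlations and ordinary regression all count such children as separate pieces of information. With positive correlation, the usual standard error of the Group 1 mean is too small. The same holds for the coefficient of any factor that is identical, or nearly so, within a family. Genetic anomaly and family socio-economic status are of that kind and are central to the secondary objective.

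There is also a practical risk. If family membership is not recorded at inclusion, it may be hard to recover, and the dependence could then not be modelled.

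**Working it through.** **Inputs from the protocol article (Sample size):** difference δ = 7, SD σ = 15, two-sided α = 5%, power 90%, 10% loss, 107 per group.

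**Inputs not in the documents (assumed):** f, the share of Group 1 children in sibling pairs, and ρ, the correlation of siblings' scores. Main range: f = 20% to 40%, ρ = 0.3 to 0.7. Wider check: f = 10% to 60%, ρ = 0.2 to 0.7. Group 2 is taken to contain no siblings.

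**Step 1. The plan's own figure.** n = 2(1.960 + 1.282)² × 15² / 7² = 96.5, so 97 per group. 97 × 1.1 = 106.7, so 107. (97 / 0.9 = 107.8 would give 108, an immaterial difference.) The plan's figure is reproduced with no allowance for related children. With 97 evaluable per group, SE = 15√(2/97) = 2.154 and power = Φ(7/2.154 − 1.96) = 90.1%.

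**Step 2. Design effect in Group 1.** With n children, fn/2 pairs each add 2ρσ² to the variance of the sum. The variance of the mean is therefore multiplied by D = 1 + fρ.
- Low end: 1 + 0.2 × 0.3 = 1.06
- High end: 1 + 0.4 × 0.7 = 1.28

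**Step 3. Primary comparison.** Only Group 1 is inflated, so the SE is multiplied by k = √((D + 1)/2).
- True type I error of the planned test = 2(1 − Φ(1.96/k))
- Power of a test with the correct SE = Φ(7/(2.154k) − 1.96)

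Low end: k = √1.03 = 1.015, error 5.35%, power 89.3%. High end: k = √1.14 = 1.068, error 6.64%, power 86.1%.

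**Step 4. A factor shared within families, analysed in Group 1.** There is no dilution: the SE is multiplied by √D, and the true error is 2(1 − Φ(1.96/√D)). Low end: √1.06 = 1.030, error 5.70%. High end: √1.28 = 1.131, error 8.32%. The 107 children carry the information of 107/1.06 = 101 down to 107/1.28 = 84 for such a factor.

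**Step 5. Range.**

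| f | ρ | D | Primary: true error | Primary: power | Shared factor: true error |
|---|---|---|---|---|---|
| 0 | any | 1.00 | 5.00% | 90.1% | 5.00% |
| 10% | 0.2 | 1.02 | 5.11% | 89.9% | 5.23% |
| 20% | 0.3 | 1.06 | 5.35% | 89.3% | 5.70% |
| 40% | 0.3 | 1.12 | 5.70% | 88.4% | 6.40% |
| 20% | 0.7 | 1.14 | 5.81% | 88.1% | 6.64% |
| 40% | 0.7 | 1.28 | 6.64% | 86.1% | 8.32% |
| 60% | 0.7 | 1.42 | 7.48% | 84.0% | 10.0% |

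**Step 6. Where the full effect does not apply.** For a predictor x whose own sibling correlation is ρₓ, the design effect is roughly 1 + fρₓρ. It equals D when ρₓ = 1, is near 1 when ρₓ is near 0, and is below 1 when ρₓ is negative. Age, activity and VO2max can differ between siblings, so their standard errors may be little affected. Proxy scores compared between groups follow Step 3, not Step 4, even if ρ is higher because the same parents rate both siblings.

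**The case against.** The strongest reply is that this is an omission in a condensed article. The full protocol or statistical analysis plan, not shown here, may deal with related children, and the choice of regression or GAM does not exclude a family term. That stands as a possibility. But the article does fix its entry criteria, sample size and tests, and followed as written with siblings enrolled, these treat related children as independent.

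Sibling enrolment is also not documented. Both siblings must be affected, aged 6 to 17 and eligible within the 18-month recruitment period. The documents give no share and no correlation. This stands, so every figure here is conditional, and at the low end (10%, 0.2) nothing of practical importance happens.

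Matching works the other way on the primary test. If controls are matched one to one and matched scores correlate by r, the variance factor falls from (D + 1)/2 to (D + 1 − 2r)/2. It returns to 1 at r = fρ/2, that is 0.03 to 0.14 over the main range. A small matching correlation could thus offset part or all of the effect on the primary test. It does nothing for analyses within Group 1.

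The shared-factor figures are unadjusted. Multivariable models that include genotype and socio-economic status would lower the residual correlation. Nor does the article bar siblings among controls, so confining the effect to Group 1 is a simplification.

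A reader might infer that all the study's intervals are too narrow, that the parent reports bear the full effect, or that 107 per group is wrong. The documents support none of these: Step 6 limits the first two, and the modest primary effect, conditional on assumed inputs, does not establish the third.

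**Conclusion.** The point holds in a limited form. The plan leaves room for related children in Group 1 and names only methods that assume independence.

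- **Primary comparison:** modest. Over the assumed main range, the true error is about 5.3% to 6.6% and power about 89% to 86%, before any offset from matching.
- **Shared factors within Group 1 (genetic anomaly, family socio-economic status):** the main concern. A nominal 5% error becomes about 5.7% to 8.3% before covariate adjustment.
- **Factors that differ between siblings, and proxy scores compared between groups:** less affected than the shared factors.

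All of this rests on assumed values of the sibling share and correlation, on pairs rather than larger sibships, and on normal approximations. With no siblings enrolled, the effect is zero. The change is worth making because the identifier is cheap at inclusion and may be hard to reconstruct later.

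**What to change.** Record a family identifier for every child at inclusion. Add to Statistical analysis that the regression models, including the group comparison fitted as a linear model, use family-clustered robust standard errors or a family random effect, and that the GAM includes a family random-effect term. Add a sensitivity analysis that keeps one child per family, chosen by a rule fixed in advance.

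For the linear models, clustered standard errors are the simpler default. In the main range there would be only about 107 × 0.2/2 = 11 to 107 × 0.4/2 = 21 sibling pairs from which to estimate a family variance, but still at least 107 − 21 = 86 families as clusters in Group 1.

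Enrolment should not be restricted to one child per family, since that would discard eligible patients with rare disorders.

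The cost is one field on the case report form, a short amendment to the analysis section and slightly wider intervals. The simple t, Mann–Whitney, Pearson and Spearman analyses do not take a family term, so they become descriptive or are replaced by clustered equivalents. If no siblings enrol, the results will be close to those of the planned analysis.

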### Primary outcome

The primary outcome is the total QoL score with the self-reported PedsQL questionnaire. The PedsQL questionnaire has four multidimensional scales: physical functioning (8 items), emotional functioning (5 items), social functioning (5 items), and school functioning (5 items). The three summary scores are: total scale score (23 items), physical health summary score (8 items), psychosocial health summary score (15 items). Each item uses a 5-point Likert scale from 0 (never) to 4 (almost always). Items are reversed scored and linearly transformed to a 0–100 scale, higher scores indicating a better QoL. This instrument was validated by Varni et al. in healthy and patient populations and its psychometric properties showed reliability, validity and responsiveness to clinical change over time [23]. The translation and cultural adaptation into French was performed by MAPI Research Institute (www.mapi-trust.org), following the international guidelines [23] and this version showed good psychometric properties [24]. We recently performed the complete psychometric validation of the French self and proxy versions of the PedsQL generic questionnaire for 8 to 12 year-old children [25]. We also found a good sensitivity of the PedsQL in several controlled prospective HRQoL studies among healthy controls and children with various chronic diseases [26–29].

In this study, three age versions of the PedsQL questionnaire will be used (e.g. 5–7, 8–12 and 13–17 years old). Parents and children will complete the QoL questionnaires during the routine paediatric cardiology consultation (inclusion visit). Children aged 8 years old and above will complete the PedsQL self-questionnaire under trained nurse supervision, as in our similar QoL studies [26–29].

### Secondary outcomes

The level of physical activity will be assessed by:The metabolic equivalent of task (MET), measured by a fitness tracker (ActiGraph GT3X accelerometer, Pensacola, FL, USA) [30]. The MET is defined as the ratio of physical activity to basal metabolic demand. The metabolic equivalence scale ranges from 0.9 MET (at rest) to 18 MET (run at 17.5 km/h). The fitness tracker will be assigned during the inclusion visit and the participants will be instructed to wear it at the waist at all times for 14 days, except during sleep and water-based activities such as swimming or bathing.The Ricci and Gagnon physical activity questionnaire, composed by 8 items (total score < 16 points: no activity; 17 to 32 points: moderate activity; 33 to 40 points: intensive activity) will be completed during the inclusion visit by the participant. Children aged 8 years old and above will complete this questionnaire under trained nurse supervision [31].The EMAPS questionnaire (motivation scale for physical activity in a health context), a 18-item motivation scale towards health-oriented physical activity recently validated in French [32]. This questionnaire will be completed during the inclusion visit by the participant. Children aged 8 years old and above will complete this questionnaire under trained nurse supervision.The exercise capacity will be assessed by a cardio-pulmonary exercise test (CPET), using the same methodology as in our previous paediatric CPET studies [5, 20, 21, 33]. The following variables will be measured: maximum oxygen uptake (VO2_max_); ventilatory anaerobic threshold (VAT); ventilatory efficiency (VE/VCO2 slope), oxygen uptake efficiency slope (OUES), and maximum oxygen pulse (VO2_max_/maximum heart rate). Exercise test procedures in all participating laboratories will be harmonized before the start of the study. All centres will use the same CPET cycle ergometer protocol, to obtain a homogeneous incremental overall duration between 8 to 12 min: a 1-min rest; a 3-min warm-up (10 to 20 watts) in increments of 10, 15, or 20 watts each minute; a pedalling rate of 60 to 80 revolutions per minute; a 3-min active recovery (20 watts); and a 2-min rest. The CPET will be considered as maximal when 3 out of the 4 following criteria will be reached: respiratory exchange ratio (RER = VCO2/VO2) ≥ 1, maximum heart rate > 85% of maximal age-predicted heart rate, limit of the patient’s tolerance despite verbal encouragement, plateau of VO2 (VO2_max_) despite the increasing exercise intensity, and patient's inability to provide a minimum pedalling frequency of 60 per minute despite verbal encouragement. The VAT will be estimated using Beaver’s method [34]. VO2_max_ and VAT values will be normalized in a percentage of the predicted VO2_max_ using reference values for cycle ergometer test in the general paediatric population [35, 36]. When the VO2_max_ does not reach criteria for maximal effort, the peak VO2 will be informed, as usual in paediatrics [37, 38].The parents-reported QoL scores will be assessed by the proxy questionnaires of the PedsQL (e.g. 5–7, 8–12 and 13–17 y.o. proxy versions) [23]. Both parents will be able to participate and will therefore separately fill out a PedsQL proxy questionnaire.

All outcomes are reported in Table 2.

**Table 2 Tab2:** Outcome measures

Primary outcome
Health-related quality of life score: PedsQL self-questionnaire (versions 5–7 years and 8–12 years for children and version 13–17 years for adolescents)
Secondary outcomes
Level of physical activity assessed by: The metabolic equivalent of task (MET) assessed by the ActiGraph GT3X accelerometer The Ricci and Gagnon physical activity questionnaire The EMAPS motivation questionnaire
CPET variables: VO2_max_ (maximum oxygen uptake) VAT (ventilatory anaerobic threshold) VE/VCO2 slope (ventilarory efficiency) OUES (oxygen uptake efficiency slope) Maximum oxygen pulse (VO2_max_/maximum heart rate)
Health-related quality of life score: PedsQL proxy questionnaire (versions 5–7 years and 8–12 years for children and version 13–17 years for adolescents)

